## Background and rationale

### Refractory freezing of gait in Parkinson’s disease

Gait dysfunction is a common and heterogeneous feature of Parkinson’s disease (PD), significantly impacting patients’ quality of life and increasing their risk for falls [1]. Common characteristics of parkinsonian gait include decreased stride length, reduced arm swing amplitude, and a flexed and stiffened trunk posture [2]. Some of these aspects of gait are improved with dopaminergic therapy or deep brain stimulation (DBS) of conventional targets such as the subthalamic nucleus (STN) or globus pallidus interna (GPi) [3]. Other deficits, such as postural instability and freezing of gait (FOG), may not respond or even worsen [4].

FOG is considered the most disabling of these gait deficits and is described as the transient and episodic failure to move forwards, despite intending to walk [5]. Patients describe feeling as if their feet are “glued” to the floor, and these episodes result in significantly decreased quality of life and contribute to falls and their related morbidities [6–8]. FOG is triggered in situations that highlight both cognitive and sensory influences on gait: during attempts to initiate stepping or turning, when navigating narrow corridors and obstacles, and when the patient is distracted or under duress [9, 10]. Conversely, these episodes frequently improve or resolve with the help of auditory or visual cues, such as a metronome set to a step cadence, or lines marked on the floor set to a desired stride length [11].

The pathophysiology of FOG is incompletely understood, but observations that it can be refractory to dopaminergic therapy suggest that it involves both dopaminergic and non-dopaminergic mechanisms [12]. FOG is associated with advanced PD [13], though it can present early [11]. While some controversy remains as to whether severe gait difficulties represent a distinct spectrum of the disease or merely a more advanced stage of the disease [14], many clinicians distinguish between tremor dominant (TD) and postural instability and gait difficulty dominant (PIGD) subtypes of PD, both in terms of their clinical prognoses as well as their management [15]. FOG is predominantly seen in the PIGD subtype and has an inconsistent response to levodopa or DBS. The development of an effective treatment for FOG remains a priority in the field.

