**Fig. 2 Fig2:**
[figure not shown]
Flow chart of study outline

Suitable eligible patients will be screened for study participation and begin the consenting process, where the study objectives and the risks and benefits of participating are explained to them. Informed consent forms for the study will be filled out by subjects to confirm enrollment and they will undergo a baseline assessment, including a thorough neurological and neuropsychiatric examination, as well as standardized subjective and objective gait assessments. The Columbia Suicide Severity Rating Scale is included during screening given the known risk of suicidality with DBS for PD [51]. After enrolment and baseline evaluation, subjects will be consented for surgery prior to bilateral implantation of DBS electrodes in the CnF, with a post-operative CT scan to localize final electrode positions. For ethical reasons, all subjects will receive active stimulation beginning at 2 weeks post-implantation and will undergo repeated gait assessments in the clinic at 2-, 6-, 12-, and 24-weeks post implantation (Table 1). Gait assessment tests will be performed on medication, with DBS on and off, and assessors will be blinded to whether the DBS is on or off to minimize the risk of bias. A more detailed kinematics and EMG gait assessment, using the Nexus system (Vicon Motion Systems Ltd) will take place at study onset and conclusion. At study conclusion, subjects will decide whether they want to continue with stimulation or discontinue stimulation; in both cases, they will continue to receive their usual standard care and follow up with their neurologist.

**Table 1 Tab1:** Detailed study schedule

Assessment	Visit 1	Visit 2	Visit 3	Visit 4	Visit 5	Visit 6	Visit 7	Visit 8	Visit 9
	Screen	Baseline assessment	Surgical screening	Surgery	2-week F/U	6-week F/U	12-week F/U	24-week F/U	25-week F/U
**Screening ICF**	X								
**Pre-op work up**^*^ **(CBC, CMP, β-hCG, INR/PTT/PT, U/A, EKG, CXR)**	X		X						
**Neuropsychiatric evaluation (including MDRS and BDI)**	X	X	X		X	X	X	X	
**Columbia Suicide Severity Rating Scale**	X	X	X		X	X	X	X	
**Gait assessment**	X	X			X	X	X	X	
**MDS-UPDRS**	X	X			X	X	X	X	
**FOG Questionnaire**		X			X	X	X	X	
**Timed Up and Go test**		X			X	X	X	X	
**Velocity test**		X			X	X	X	X	
**Variability test**		X			X	X	X	X	
**PDQ-39**		X	X		X	X	X	X	
**PDQL**		X	X		X	X	X	X	
**Brief pain history and NPSI**		X	X		X	X	X	X	
**Surgical ICF**			X						
**MRI**			X						
**Device implantation**				X					

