### Participants

We are actively screening and recruiting patients for this study from the Movement Disorders Clinic at the University of Miami Hospital. As this is a pilot study, we plan to enroll 4 patients with PD with levodopa-resistant FOG. A movement disorder neurologist will assess the eligibility of a patient based on the inclusion and exclusion criteria are detailed below.

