### Inclusion criteria

Age 40–75FOG is the primary complaint despite optimized dopaminergic therapy by a movement disorder neurologistClinical observation of FOG in the ON/OFF states by a movement disorder neurologistPD stage 3 with good response to levodopa (defined as greater than 20% improvement in MDS-UPDRS score), except for severe gait disorderPD stage 3 with severe gait dysfunction and predominant axial symptoms defined as TD/PIGD ratio ≤ 0.90 (mean value of MDS-UPDRS items 2.10, 3.15a, 3.15b, 3.16a, 3.16b, 3.17a, 3.17b, 3.17c, 3.17d, 3.17e, and 3.18 divided by the mean value of MDS-UPDRS items 2.12, 2.13, 3.10, 3.11, and 3.12) [15] and FOGQ score> 12Minimal tremor, bradykinesia, and rigidity, or well controlled with levodopa.Agrees to full 6-month study participation

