### Assessments

The following assessments will be completed to screen for study/surgical eligibility:
History and physical exam, including a neurological and clinical gait assessmentBlood pressure and postural dropPre-operative lab work, including 12-lead electrocardiogram and chest x-rayNeuropsychiatric evaluation, including the Mattis Dementia Rating Scale-2, Beck Depression Inventory II, and the Columbia Suicide Severity Rating Scale

The following assessments will be completed prior to DBS implantation as well as at each clinic visit post-implantation:
MDS-UPDRSFOG QuestionnaireTimed Up and Go (TUG) testInstrumented gait assessment (Opal Inertial measurement unit, APDM Inc., Portland, OR) measuring:
Stride length (average over 2-min walk)Velocity (average over 2-min walk)Gait variability (measured over a 2-min walk)360° clockwise and counterclockwise turn on the spot (time and number of steps)The Parkinson’s Disease Questionnaire (PDQ-39) and the Parkinson’s Disease Quality of Life Questionnaire (PDQL)Columbia Suicide Severity Rating ScaleA brief pain history and Neuropathic Pain Symptom InventoryBlood pressure and postural drop assessed in the off and on DBS stimulation state.

At study conclusion, patients will undergo a detailed kinematics gait assessment using the Nexus system (Vicon Motion Systems Ltd) and surface EMG recordings in the lower limbs.

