### Secondary outcomes

Percent change in FOG Questionnaire (FOGQ), Parkinson’s Disease Questionnaire (PDQ-39), and the Parkinson’s Disease Quality of Life Questionnaire (PDQL)Percent change in Movement Disorders Society Unified Parkinson’s Disease Rating Scale (MDS-UPDRS) Part III across study visits relative to pre-operative baseline evaluation.Percent change in number of falls (between baseline and final gait testing sessions, and on item 13 of UPDRS III)Percent change in gait velocity with and without CnF DBSPercent change in muscle electromyogram (EMG) amplitude during gait testing at study conclusion between CnF DBS on and off conditions

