## Discussion

PD patients with FOG that is refractory to dopaminergic therapy have limited therapeutic options. Our study protocol aims to test the safety, feasibility, and preliminary efficacy of a novel brainstem target to alleviate FOG. Our strategy is based on a careful revisiting of classical animal studies [16], newly emerging optogenetics data [47], and a recent clinical study [43], all of which suggest that optimizing the location of DBS within the MLR could significantly improve the effect of DBS on this gait network. While some have pointed to the inconsistent outcomes of previous PPN DBS studies as a reason to abandon this approach altogether [41], that subsets of patients with FOG show significant improvement with DBS in this region suggests that refinement of methodology may be important. Through this and future larger scale studies, we hope to determine if CnF DBS could be an effective therapy for FOG and gait dysfunction in other neurodegenerative disorders.

A strength of this study is the novel use of directional electrodes to deliver DBS to this midbrain region. As a complex area comprised of numerous interleaving fiber tracts and structures, the ability to steer current would be important in optimizing therapeutic effects while mitigating stimulation-induced side effects. Limitations of this study include the small sample size, given the preliminary nature of this study, and the lack of a control cohort. Additionally, as some patients with DBS in this region feel mild paresthesias with stimulation, complete double blinding of DBS status during gait assessments may be impossible. Finally, there are limitations related to the studying of FOG itself, including potential heterogeneity of pathobiology, and difficulty in eliciting FOG in the clinical setting. We hope to mitigate these difficulties through our rigorous inclusion/exclusion criteria, and by using known triggers for FOG during gait assessments, if necessary.

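### The falls outcome is a percent change that is undefined at zero baseline falls, leaves its counting window unclear, and mixes a count with a rating item that does not match the protocol's own numbering

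*Protocol article*

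**What the plan says.** The protocol article, Secondary outcomes, lists "Percent change in number of falls (between baseline and final gait testing sessions, and on item 13 of UPDRS III"). This one entry names two sources, a number of falls and a scale item, and puts both on the percent-change scale.

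Under Participants, "we plan to enroll 4 patients with PD with levodopa-resistant FOG".

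Under Assessments, the list introduced by "The following assessments will be completed prior to DBS implantation as well as at each clinic visit post-implantation" includes the MDS-UPDRS, the FOG Questionnaire, Timed Up and Go and the instrumented gait measures. It does not name a fall count or a recall period, and neither does Table 1. Table 1 does place the MDS-UPDRS and a gait assessment at baseline and at 2, 6, 12 and 24 weeks, and gait kinematics at baseline and week 25.

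The Inclusion criteria cite MDS-UPDRS items by part and number. The denominator of the eligibility ratio is "the mean value of MDS-UPDRS items 2.12, 2.13, 3.10, 3.11, and 3.12".

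Two remarks bear on how often falls may be seen. The background says of freezing that "these episodes result in significantly decreased quality of life and contribute to falls and their related morbidities", and the Discussion lists among the study's limitations "difficulty in eliciting FOG in the clinical setting". No fall rate is stated anywhere.

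**The concern.** Falls are the consequence of freezing that patients feel most directly, and a pilot should tell the next trial how to measure them. As worded, the outcome may not produce a value for every patient, and two analysts could compute different things from the same data. One could count falls during the first and last testing sessions. Another could count falls over the months between them. A third could report the change in a scale item as though it were a fall count. With four patients there is no averaging to absorb a lost or mislabelled value.

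**Working it through.** The plan gives no fall rate, variance or sample-size figure for this outcome, so there is no stated number to reproduce. The check has three parts.

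**1. What is being counted.** Set the wording against the schedule.
- Falls during the sessions: the comparison is between two clinic visits. Which visit is final is open, since Table 1 has a gait assessment at week 24 and gait kinematics at week 25.
- Falls accumulated between the sessions: this gives one on-study total. The text names no pre-operative period of the same kind, so percent change has no denominator.

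**2. The percent-change scale.** For patient *i* with baseline count *B* and final count *F*, percent change = 100 × (*F* − *B*)/*B*.
- If *B* = 0, it is undefined whatever *F* is. The regression imputation under Handling of missing data concerns missing observations; here both counts are observed and the ratio does not exist.
- If *B* = 1, each fall more or fewer moves the result by 100/1 = 100 percentage points.
- One undefined value out of four is 1/4 = 25% of the data.

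The number of patients affected depends on the baseline mean per counting window, which must be assumed. Under a Poisson count with mean λ, P0 = exp(−λ), the expected number undefined is 4 × P0, and the chance of at least one is 1 − (1 − P0)^4. For λ = 1: P0 = exp(−1) = 0.368; 4 × 0.368 = 1.47; 1 − 0.632^4 = 0.840.

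| Assumed mean falls per window | P0 | Expected undefined of 4 | P(at least one undefined) |
|---|---|---|---|
| 0.1 | 0.905 | 3.62 | >0.99 |
| 0.5 | 0.607 | 2.43 | 0.976 |
| 1 | 0.368 | 1.47 | 0.840 |
| 2 | 0.135 | 0.54 | 0.441 |
| 5 | 0.007 | 0.03 | 0.027 |

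A zero baseline is the likelier result for a patient only when exp(−λ) > 0.5, that is λ < ln 2 = 0.69.

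If falls cluster in some patients, zeros are more common at the same mean. With a negative binomial count and an assumed dispersion k = 0.5, P0 = (1 + λ/k)^(−k). At mean 1, P0 = 3^(−0.5) = 0.577 and 4 × 0.577 = 2.31 values are undefined. At mean 5, P0 = 11^(−0.5) = 0.302 and 1.21 are undefined.

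**3. The scale item.** Secondary outcomes point to item 13 of Part III. In the part-and-number form of the Inclusion criteria that would be 3.13, which the article never lists; the only item 13 it lists is 2.13, in Part II. Whichever is meant, a rating item is an ordinal score and cannot supply a number of falls. Its percent change is also undefined at a baseline score of 0. If a Part III item is truly intended, it already sits inside the preceding secondary outcome, percent change in MDS-UPDRS Part III.

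**The case against.** The strongest reply is that the plan may work well enough in practice. Enrolled patients have severe gait dysfunction and a FOGQ score above 12, freezing is said to contribute to falls, and known triggers may be used during gait assessments. If falls are counted over weeks in frequent fallers, almost every patient has a usable baseline: at a Poisson mean of 5, only 0.03 of 4 values are lost. The MDS-UPDRS and the gait sessions are scheduled at baseline and through week 24, and a condensed article may leave a falls form or recall period to the full protocol. Falls are one of several secondary outcomes in a pilot aimed at safety and feasibility. Adverse events are listed, and unexpected, non-transient worsening of gait is among the stoppage rules.

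Much of this stands, and it rules out three stronger readings.
- A reader might infer that baseline falls are probably zero and that most patients will have no value. That needs a fall rate the documents do not give, and their remarks point both ways.
- A reader might infer that nothing is collected. The scale and the sessions are scheduled, and silence in an article about a form is no defect.
- A reader might infer that the cited item has nothing to do with falls, or that the article's shorthand UPDRS III means a different scale. The article does not say what the item measures, and Data analysis uses the same shorthand.

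The reply does not reach what is printed: a ratio that fails at zero, a phrase with two meanings, and a score offered as a count. A form held elsewhere would not by itself cure these.

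**Conclusion.** The point holds as a fault in the definition of one secondary outcome. Percent change is undefined for any patient with no baseline falls and very coarse for a patient with one. The counting window is ambiguous, and on one reading there is no baseline count. The item reference does not fit the protocol's own numbering and names an ordinal score as a source for a count.

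The size cannot be fixed from the documents. It runs from about 3.6 of 4 values undefined at an assumed mean of 0.1 falls per window, through 1.5 at 1 fall, to 0.03 at 5 falls. These figures assume independent patients and Poisson counts; clustering of falls would raise the loss. The documents do not support saying that the outcome fails for most patients or that a safety signal would be missed. The primary safety and feasibility aims are not affected. The change is worth making because it is cheap and the pilot is meant to inform a larger trial.

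**What to change.** - Drop percent change for falls. Report each patient's fall count and the absolute change in rate, for example falls per 4 weeks, listed individually for the four patients.
- State one counting window of equal length before surgery and before the follow-up visits, obtained by recall or by a log reviewed at existing visits. Four weeks is one length that fits: stimulation starts at week 2, and the gaps to the next visits are 6 − 2 = 4, 12 − 6 = 6 and 24 − 12 = 12 weeks. Other lengths would serve if they are equal before and after.
- If falls during testing sessions are also wanted, report them separately and name the sessions, including whether the final one is week 24 or week 25.
- Check the cited item against the scale form, correct the reference by part and number, and report it as its own ordinal outcome with raw scores and change.

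The cost is a short falls question or log at visits that already exist, plus a rewording of the outcome. Recruitment opened in April 2020, so any patient already implanted would have no pre-operative count collected under the new definition, and the report should say so.

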### Kinematic and EMG evaluation of gait

Lower-limb gait kinematics and EMG will be evaluated with and without DBS in study subjects (*n* = 4). Subjects will be fitted with fifteen reflective markers that will be tracked at 100 Hz with a 10-camera Nexus system (Vicon Motion Systems Ltd) attached bilaterally to the first and fifth distal phalange of the foot, lateral malleolus, calcaneus, lateral femoral epicondyle, anterior superior iliac spine, and the mid-shank and mid-thigh. A reflective marker will also be placed on the lower back region overlying the sacrum. EMG surface electrodes will be placed over the tibialis anterior (TA) as well as the lateral gastrocnemius (LG). Subjects will be asked to walk along a 25-foot path at a constant, regular walking pace both without and then with optimal DBS configuration settings (CnF L on/CnF R on), DBS OFF (CnF L off/CnF R off), DBS RIGHT Only (CnF L off/CnF R on), and DBS LEFT only (CnF L on/CnF R off) repeating each condition twice. Kinematic and EMG signals will be recorded during each trial while the subjects walk for 25 ft. and averaged for each test condition.

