### DBS programming

Intraoperative stimulation parameters will be used to guide initial programming. Programming sessions will have heart rate, blood pressure, respiratory rate, and blood oxygenation saturation monitoring to mitigate the risk of adverse cardiorespiratory events related to stimulation. Additionally, low frequencies will initially be explored with patients until an adequate stimulation amplitude is found where gait initiation is under volitional control. Stimulation amplitude will then be increased until an adequate gait speed is achieved. If this is not immediately apparent, stimulation amplitude will be increased to just below the threshold for onset of side effects. Based on other studies, cyclic stimulation with continuous daily stimulation and night arrests will be the default protocol to avoid habituation and waning of effects [43, 54]. Current steering will be used to increase the therapeutic window and maximize chances of therapeutic benefit.

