### Data analysis

The primary goal of this pilot study is to assess the safety and feasibility of delivering DBS to the CnF in PD patients with refractory FOG and thus will only involve 4 subjects. We believe this number of subjects will provide adequate data on safety and feasibility for a larger study. However, assessment of trend toward efficacy will be performed for the secondary outcomes. One-way ANOVA will be used to compare percent improvement in gait velocity for the four different DBS configurations (L CnF off/R CnF off, L CnF off/R CnF on, L CnF on/R CnF off, L CnF on/R CnF on) at each clinic visit, with the Tukey Honest Significant Difference post hoc test to compare configurations. The same test will be used to compare changes in EMG amplitude between the four DBS configurations at the final gait assessment at the study’s conclusion. One-way ANOVA with repeated measures will be used to compare changes in the UPDRS III, FOG Questionnaire, PDQ-39, and PDQL over the multiple time points of the study.

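### The kinematic and EMG walks are described as DBS off and then on, with no counterbalancing, so drift within the session can pass for a stimulation effect

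*Protocol article*

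**What the plan says.** The section on kinematic and EMG evaluation of gait has each patient walk a 25-foot path "both without and then with optimal DBS configuration settings", which it defines as both sides on. The same sentence then adds DBS OFF, RIGHT only and "DBS LEFT only (CnF L on/CnF R off) repeating each condition twice". Signals are "averaged for each test condition". Nothing is said about randomising, balancing or concealing the order.

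These walks supply a named secondary outcome, the percent change in EMG amplitude "during gait testing at study conclusion between CnF DBS on and off conditions". The Data analysis section names a one-way ANOVA with Tukey comparisons for gait velocity and continues: "The same test will be used to compare changes in EMG amplitude between the four DBS configurations at the final gait assessment". No order or period term is mentioned.

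The Study design and overview section says gait tests are done on medication with DBS on and off, and that "assessors will be blinded to whether the DBS is on or off to minimize the risk of bias". The next sentence introduces this session: "A more detailed kinematics and EMG gait assessment, using the Nexus system". It does not say whether the blinding extends to it.

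**The concern.** If off always comes before on, order and stimulation cannot be told apart. Patients may warm up, tire, or move along their levodopa cycle during the session. Whatever that does to gait or muscle activity enters the on-minus-off difference in every patient, and neither more patients nor averaging the repeats removes it. There is no control cohort to show what the drift would have been.

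A known sequence also tells staff which state they are observing. The signals come from cameras and surface electrodes, so this would act mainly through instructions, encouragement and signal processing, not through a rating.

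What is at stake is the trend-toward-efficacy reading of the EMG and kinematic contrasts, which is meant to inform a larger trial. Data collected in one fixed order cannot be disentangled afterwards.

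**Working it through.** The protocol gives no figure to reproduce here. The check asks how much drift each reading of the text would put into the contrasts.

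**Inputs from the document:** four patients; four configurations (both on, OFF, RIGHT, LEFT); each condition walked twice.

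**Assumptions:** equally spaced walks and a linear drift of d per walk, of unknown size and sign. Then

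bias(configuration minus OFF) = d × (mean walk position of the configuration − mean walk position of OFF).

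| Reading | ON − OFF |
|---|---|
| OFF, OFF, ON, ON | (3.5 − 1.5)d = 2d |
| OFF, ON, OFF, ON | (3 − 2)d = 1d |
| OFF first and ON last of four, repeats together | (7.5 − 1.5)d = 6d |
| ON, OFF, RIGHT, LEFT as listed, with the first off walk taken as the baseline visit | (1.5 − 3.5)d = −2d |
| Off, ON, OFF, RIGHT, LEFT as five pairs, both off pairs pooled | (3.5 − 3.5)d = 0 |

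In the fourth row, RIGHT − OFF is (5.5 − 3.5)d = 2d and LEFT − OFF is (7.5 − 3.5)d = 4d. In the last row they are (7.5 − 3.5)d = 4d and (9.5 − 3.5)d = 6d. So even the reading that clears ON − OFF leaves the one-sided configurations biased.

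**Effect on a test.** As an illustration, take a paired t test at n = 4 (two-sided 5%, 3 df) with no true effect. Let the total drift in the contrast be D, in SDs of the within-patient difference. The noncentrality is D × √4 = 2D.

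| D (assumed) | Rejects with no true effect |
|---|---|
| 0 | 5% |
| 0.25 | 6.5% |
| 0.5 | 11% |
| 1.0 | 29% |
| 1.5 | 53% |

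The planned test is a one-way ANOVA, so these rates show the pattern and are not predictions for this trial.

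**Balanced order.** One Williams square is: OFF, ON, LEFT, RIGHT; ON, RIGHT, OFF, LEFT; RIGHT, LEFT, ON, OFF; LEFT, OFF, RIGHT, ON. OFF falls in positions 1, 3, 4 and 2 across the four sequences, and ON in positions 2, 1, 3 and 4, so both average 2.5. The same holds for RIGHT and LEFT. Each of the 12 ordered pairs of neighbours occurs once. Linear-drift bias is therefore 0 for every contrast with OFF, and any additive period effect common to the patients cancels.

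With subject, period and configuration fitted to the 16 condition means, 15 − 3 − 3 − 3 = 6 residual df remain. If one patient is missing, 11 − 2 − 3 − 3 = 3 remain.

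**Concealment.** A known off-then-on order identifies the off/on pair with certainty. Under a random, withheld order, the chance of guessing from sequence alone which of four positions is OFF is 1 in 4.

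**The case against.** The strongest reply is that the sentence is garbled and may not be a running order at all. OFF is named separately after both-on, and Table 1 schedules kinematics at Visit 2, before implantation, and at Visit 9. The off-then-on phrase could therefore mean baseline and then implanted. Taken literally as five bouts, off brackets on and linear drift cancels in that one contrast. This stands as a limit on certainty: the full order is unclear. It does not remove the point, because no reading provides counterbalancing and most leave drift in at least one contrast.

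The blinding conflict is also an inference. Blinding is stated for the gait assessment tests, just after the clinic visits are listed, and the kinematic session is introduced next. It is called a gait assessment and is not exempted, so the inference is reasonable, but it is not a stated contradiction. The Discussion already concedes incomplete blinding, though only because of paresthesias.

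A reader might infer three further things that the document does not support:

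- **That gait velocity is biased by a known amount.** Velocity is analysed at each clinic visit, for which no running order is stated, and the document gives no drift figure.
- **That this is the trial's only blinded on/off evidence.** Gait tests with DBS on and off, under blinded assessors, are planned at four clinic visits.
- **That settings are tuned on the outcome just before it is scored.** The programming section does say "Stimulation amplitude will then be increased until an adequate gait speed is achieved", but Table 1 does not give the order of programming and testing within a visit.

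**Conclusion.** The point holds as a moderate one. The only order stated for these walks is off before on, no balancing is described, and the analysis as described cannot separate drift from stimulation. For a simple off/on pair the bias is one to two times the drift per walk. Across the readings tabulated, the on-minus-off bias runs from −2d to 6d. These sizes rest on linear drift and equal spacing. The direction is open, since practice would favour on and fatigue would work against it.

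The defect is confined to the kinematic and EMG session and its exploratory contrasts in a four-patient pilot. The primary safety and feasibility endpoints and the stoppage rules do not depend on it.

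**What to change.** Before the final gait sessions:

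1. Rewrite the kinematic and EMG section so that the four configurations are each listed once, and say separately what is done at baseline.
2. Assign the four patients at random to the four sequences of a 4x4 Williams square, run both repeats within each period, and keep the same interval after every switch.
3. Have an unblinded programmer set the device, and withhold the order from assessors and from those who process the signals.
4. Include subject and period, with configuration, in the analysis of these walks.
5. As a low-cost precaution, vary the on/off order at the clinic visits too, where none is stated.

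The cost is a four-line allocation list and a few more device switches. No patients, visits or procedures are added. If a patient drops out the square is no longer balanced. Period can still be fitted, but with 3 residual df instead of 6.
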